## What are the proposed practical arrangements for allocating participants to trial groups?

Patient recruitment will occur at Hamilton Health Sciences, St. Joseph’s Healthcare Hamilton, and Kingston Health Sciences. All surgeons who perform elective non-bariatric surgery at these sites will be made aware of the study via workshops and internal communications. Patients will be identified by the surgeons, their administrative assistants, and/or study investigators at the time of referral, at the time of their initial preoperative consultation, or some time following their initial preoperative consultation. Surgeons and/or other clinicians within a patient’s circle of care will introduce the study to participants at the time of their preoperative visits or sometime thereafter. Patients may also reach out directly to study investigators via the contact information provided on the study poster should they choose. Patients meeting inclusion criteria based on a review of their electronic medical record, which will only be accessed by persons within the circle of care or researchers that have obtained permission from the patient, will have their contact information (i.e., email and phone number) recorded and provided to designated research personnel at the time of their initial surgical consultation in clinic. This email contact information will then be passed into a novel automated clinical trials platform developed by Phelix AI©. This platform will automatically send an electronic version of the written informed consent document to the patient as well as a link to schedule an appointment in the following 1-2 days with the research team to discuss the informed consent document via telephone. If the Phelix AI© platform identifies that the patient does not have an accessible email address, this will trigger a notification to the research team and prompt them to call the patient by telephone. At the time of initial contact between the study personnel and patient, the study will be introduced, eligibility will be confirmed. Patients will be provided with the opportunity to ask questions about the previously circulated ICF, and if they have yet to review the document, they will review the document in its entirety with the research team at the time of the telephone contact. If, at the end of this process, patients are understanding of the material risks and benefits of participation, and wish to be enrolled in the study, they will sign the ICF and subsequently be randomized to one of the two arms in this parallel RCT. Following ascertainment of written informed consent, patients will be randomized via a web-based randomization system (randomization.net) in a 1:1 fashion to receive either standard of care plus preoperative VLED or standard of care alone. Randomization will be according to variable block sizes of four and six and will be stratified according to centre.

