## What is the proposed duration of treatment period?

The current protocol in use at our local Bariatric Surgery Center of Excellence (i.e., St. Joseph’s Healthcare Hamilton) utilizes four doses of Optifast® 900 or Medimeal® daily and the total length varies between one and three weeks based on preoperative liver size and BMI. To standardize the approach for non-bariatric surgery, we propose an intervention period of three-weeks. Patients will start the intervention period three weeks and one day prior to their operative date, and the last day of the intervention will be the day prior to surgery. Our systematic review identified protocols varying from 0.46-26 weeks that were safe and efficacious, and thus we are confident that our intervention period is appropriate.^19^ Similarly, the current protocol in use at our local Bariatric Surgery Center of Excellence is in keeping with the findings of our systematic review in terms of VLED liquid formulation product and caloric intake target. In our systematic review and meta-analysis, Optifast® was the most commonly studied VLED liquid formulation (35.7% of included studies) and daily target caloric intake ranged from 450-1400kcal per day.^19^ As mentioned previously, the present study will also use the Optifast® 900 or Medimeal® and will aim to provide a total of approximately 900 kcal per day to participants.

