## What is the proposed frequency and duration of follow up?

Patients will attend follow up with their respective surgeons as per the surgeon’s clinical follow-up schedule for the given procedure. From a research perspective, the patient follow-up protocol will be implemented following initiation of the VLED. See Figure 1 for the SPIRIT diagram depicting the research follow-up protocol. Patients will be followed for a period of approximately 8 weeks. Patients will have in-person baseline measures, including weight, height, waist circumference, hand grip strength, and symptom screening at the time of preoperative VLED initiation, the day of their surgery, and at 30-days following the date of their surgery. On the day of their surgery, patient data will also be collected with regards to compliance with the preoperative VLED. At the one-month follow-up, patients will also complete standardized follow-up questionnaires that will focus on adverse events, symptoms, and postoperative recovery, as well as the 36-Item Short Form Survey (SF-36). Electronic medical records will be reviewed at thirty-days postoperatively to assess for postoperative morbidity and mortality. Both the clinical and research follow-up will be consistent regardless of the arm the patient is allocated to.

| **Activity** | **Before Randomization** | **-23** | **After Randomization** | | | |
| --- | --- | --- | --- | --- | --- | --- |
|  | **-60 to -23** |  | **-23 to -2** | **-2 to 0** | **0 to discharge** | **+30** |
| Eligibility assessment | X |  |  |  |  |  |
| Informed consent | X |  |  |  |  |  |
| Randomization |  | X |  |  |  |  |
| Intervention (i.e., VLED) |  |  | X |  |  |  |
| Baseline demographic data | X |  |  |  |  |  |
| Operative data collection |  |  |  | X |  |  |
| Baseline anthropometrics (including hand grip strength) | X |  |  |  |  |  |
| Post-intervention anthropometrics |  |  |  | X |  |  |
| Post-surgical anthropometrics |  |  |  |  |  | X |
| Intervention-associated adverse events |  |  | X | X | X | X |
| Postoperative morbidity |  |  |  |  | X | X |
| Surgeon perceived difficulty |  |  |  | X |  |  |
| QoL assessment (i.e., SF-36) | X |  |  | X |  | X |
| Intervention adherence |  |  | X | X |  |  |
| Follow-up completion |  |  |  |  |  | X |

*Figure 1.* SPIRIT figure for participant timeline

*VLED, very low energy diet; QoL, quality of life*

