4. Follow-up completion: Defined as completion of the pre-VLED, preoperative, and thirty-day postoperative visits, along with complete anthropometric measures and study questionnaires. A follow-up completion rate of greater than 90% will support the feasibility of a larger RCT. A follow-up completion rate of 80-90% will be considered feasible with modifications for the adequately powered RCT. A follow-up completion rate of less than 80% will suggest that a larger RCT is not feasible.

Safety Outcomes:

The primary safety outcome will be adverse events deemed secondary to the Optifast® 900 or Medimeal® programs. The adverse events will be recorded as dichotomous outcomes and described as either minor or serious, in a similar fashion to the OPTIWIN Study; the largest medical weight loss RCT evaluating Optifast®.^41^ Standardized definitions for minor and major adverse events are described in “Adverse Events” associated document. We will also measure patient frailty with grip strength at the time of anthropometric measurement.^43^

Clinical Outcomes:

The efficacy outcomes will include:

1. Overall 30-day postoperative morbidity. This will be defined as any deviation from the usual postoperative course within 30-days of the index operation and will be a composite of system-specific complications (see “Trial Outcome Definitions” document)
2. 30-day system-specific complications (see “Trial Outcome Definitions” document)
3. 30-day postoperative mortality
4. Preoperative weight loss. Preoperative weight loss will be assessed by measuring the post-VLED weight on the date of surgery and adjusting for the baseline weight in kilograms, as measured in a standardized fashion by a blinded research assistant.
5. Operative time. Operative time was chosen as an outcome as it is a commonly used objective surrogate for operative difficulty across various types of surgery.^44–46^ It has been used in previous bariatric RCTs as the primary outcome.^47^ Operative time will be measured as the time between first skin incision and closure of the last surgical wound in minutes and will be retrieved from the patient electronic medical record.
6. Intraoperative blood loss. This will be measured in milliliters and will be ascertained from the patient chart.

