**Describe the trial steering committee and if relevant the data safety and monitoring committee.**

[name] will be the principal investigator for the present RCT, and part of his responsibilities will be to oversee day-to-day trial management. He will be supported by a steering committee, as well as research assistants and biostatisticians. The steering committee will be involved through study inception until study completion. The steering committee will oversee design, data collection, data management, interpretation of the data, and manuscript generation. This committee will hold the primary responsibility for publication of the trial results. It will be comprised of both clinical and methodologic experts; specifically, the principal investigators, national leaders, and individuals with knowledge in specific areas or in clinical trial methods. [name] will meet with the steering committee at least once during the planning, recruitment, and close-out phases of the trial, and at any other time point as deemed necessary by the principal investigators.

To provide more frequent oversight of the study, a subset of the steering committee will constitute the operations committee. This committee will be composed of a select group of investigators chosen for their specific expertise and experience. The operations committee is ultimately responsible for all decisions regarding the design and conduct of the trial. Outcome adjudication committees and statistical analysis sub-committees blinded to treatment allocation will be formed and oversee data collection, extraction, and analysis. An equity, diversity, and inclusion (EDI) sub-committee will be formed to ensure that all relevant EDI aspects of this trial are identified and managed.

An independent Data Monitoring Committee (DMC) will be established and lead by an independent physician to monitor and adjudicate adverse events throughout the trial. Occurrence of all serious adverse events will be collected, where applicable, in keeping with laws and regulations governing the study site. All serious adverse events will be fully documented on appropriate case report forms outlining onset, duration, treatment required, outcome, and action taken. These data will be iteratively evaluated by the DMC and should there be cause for concern for patient safety moving forward at any point in the trial, they will consult with the principal investigators to discuss premature termination of the study.

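### The diet runs wholly before surgery, but morbidity and mortality are counted only from the operation, and no listed outcome compares all-cause events or surgery status by arm from randomisation

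*Protocol*

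**What the plan says.** Patients are allocated "in a 1:1 fashion to receive either standard of care plus preoperative VLED or standard of care alone" (Protocol, practical arrangements for allocation). The participant timeline places randomisation at day -23, and the section on the treatment period says that "the last day of the intervention will be the day prior to surgery".

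The clinical outcomes open later. Overall morbidity is the first: "This will be defined as any deviation from the usual postoperative course within 30-days of the index operation". The third is "30-day postoperative mortality". Ascertainment follows the same window: "Electronic medical records will be reviewed at thirty-days postoperatively to assess for postoperative morbidity and mortality" (frequency and duration of follow up). The timeline ticks morbidity only under day 0 to discharge and day +30: "Postoperative morbidity | | | | | X | X".

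The diet window is covered by safety recording. "The primary safety outcome will be adverse events deemed secondary to the Optifast® 900 or Medimeal® programs", graded minor or serious, and the timeline collects these events from day -23 to day +30. Adverse-event questionnaires are given at baseline, on the morning before surgery and at 30 days. Separately, "Occurrence of all serious adverse events will be collected" and passed to the data monitoring committee.

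Follow-up completion requires the pre-diet, preoperative and 30-day postoperative visits; above 90% supports a larger trial, 80-90% means feasible with modifications, and below 80% means not feasible. No feasibility, safety or clinical outcome counts operations performed, postponed or cancelled. The protocol does not say how a randomised patient without an operation enters any outcome.

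**The concern.** Whether and when a patient reaches surgery is decided after randomisation, and a three-week diet could change it. Outcomes anchored to the operation are undefined for anyone who does not have one. This also weakens the protocol's own safeguard, in its section on protecting against bias, that complete follow-up of all randomised patients preserves prognostic balance.

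Safety recording does not fill the gap. Control patients receive no product, so an outcome restricted to product-attributed events cannot be compared between arms. Serious adverse events are collected regardless of cause, but for oversight and not as a listed outcome.

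At stake are the safety answer (a stated pilot objective), the reading of the follow-up benchmark, the arm-level morbidity rates, and the aggregated morbidity that the protocol will set against the full-trial power calculation. The planned full trial has 30-day postoperative morbidity as its main comparison, so the definition carries forward.

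**Working it through.** **1. The plan's own figure.** The pilot size rests on the precision of 90% follow-up completion in 88 patients, stated as 82-95%. Wilson score interval with p = 0.90, n = 88, z = 1.96:

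- centre = (p + z²/2n)/(1 + z²/n) = (0.900 + 0.0218)/1.0437 = 0.883
- half-width = z·√[p(1-p)/n + z²/4n²]/(1 + z²/n) = 1.96 × 0.03386/1.0437 = 0.0636
- interval 82.0% to 94.7%, which reproduces the stated range.

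**2. Time outside the count.** From randomisation (day -23) to day +30 is 53 days. Morbidity and mortality cover days 0 to +30. The uncounted part is 23/53 = 43%, and it contains the whole diet.

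**3. Effect on follow-up completion.** Suppose every other patient completes follow-up and each unoperated patient fails it for want of a postoperative visit.

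| Unoperated of 88 | Completion | Band |
|---|---|---|
| 8 | 80/88 = 90.9% | supports a larger trial |
| 9 | 79/88 = 89.8% | feasible with modifications |
| 18 | 70/88 = 79.5% | not feasible |

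The benchmark can therefore be missed through non-operation alone, and the outcome as defined would not show that this was the cause.

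**4. Illustrative effect on the diet-arm morbidity rate.** The documents give no rate of non-operation and no morbidity rate, so all inputs here are assumptions: no true diet effect; true rate p = 25% or 15%; a fraction q = 5% of the diet arm not operated on (about 2 of 44) and no controls; would-be morbidity r = 40% or 50% in those patients. The three possible handling rules are:

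- operated patients only: (p - qr)/(1 - q)
- all randomised, unoperated counted as event-free: p - qr
- all randomised, non-operation counted as an event: p - qr + q

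| p | r | Operated only | Event-free | Counted as event |
|---|---|---|---|---|
| 25% | 40% | 24.2% (-0.8) | 23.0% (-2.0) | 28.0% (+3.0) |
| 25% | 50% | 23.7% (-1.3) | 22.5% (-2.5) | 27.5% (+2.5) |
| 15% | 40% | 13.7% (-1.3) | 13.0% (-2.0) | 18.0% (+3.0) |
| 15% | 50% | 13.2% (-1.8) | 12.5% (-2.5) | 17.5% (+2.5) |

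Percentage-point shifts are in brackets. The direction depends on a rule that the protocol leaves open. If non-operation were equal in both arms and fell on patients of the same risk, the between-arm shift would vanish, though the level of both rates would still move.

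**5. Effect on a pooled rate.** If the aggregated morbidity is read as both arms pooled, with equal arms, the operated-only rate is (p - qr/2)/(1 - q/2). For p = 25%, r = 40% this is 0.240/0.975 = 24.6% (-0.4 points); for p = 15%, r = 50% it is 0.1375/0.975 = 14.1% (-0.9 points). Counting the unoperated as event-free shifts it by qr/2, that is 1.0 to 1.25 points.

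**The case against.** The strongest defence is that this is a feasibility pilot. It tests nothing, reports binary outcomes as proportions with intervals, and plans no between-arm odds ratio for morbidity. A shift of 1-2 points could not be seen with 44 patients per arm: the Wilson interval for 11/44 is about 15-39%. Counting from the operation matches the stated research question. Handling of patients without an operation may be settled in the outcome-definitions document or the full-trial analysis plan, neither of which is shown. Diet-window events are not lost, and follow-up completion partly registers missed surgery.

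Much of this stands, and it limits the point. A reader might infer that the protocol prescribes a comparison restricted to operated patients, and hence that the diet will falsely appear protective. The documents do not support that. Restriction to operated patients is one implication of the outcome definition and not a written rule; counting the unoperated as event-free is another. The direction and size of any bias rest on assumed, one-sided non-operation. A reader might also infer that the full-trial figure of 1,158 lacks an allowance for patients who miss surgery. That cannot be checked, because its inputs are in a document not shown.

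What the defence does not answer is that the counting window and the attribution limit are fixed in this protocol, and that no listed outcome gives either an all-cause comparison from randomisation or the surgery status by arm.

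**Conclusion.** The point holds as a gap in the outcome definitions, worth correcting but not fatal to the pilot. About 43% of the post-randomisation period, including the entire intervention, lies outside the morbidity and mortality counts, and what is listed for that period cannot be compared like for like between arms. Unoperated patients have no defined clinical value and are mixed with ordinary loss in follow-up completion, where nine of 88 are enough to miss the benchmark.

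Either implied reading can bias the arm-level rates and the rate carried to the full-trial calculation. The documents do not allow the amount to be estimated. Under the assumed 5% non-operation confined to the diet arm, with would-be morbidity of 40-50%, the diet-arm rate falls by 0.8-1.8 points if only operated patients count and by 2.0-2.5 points if the unoperated count as event-free. No claim about a false efficacy finding follows from this pilot.

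**What to change.** Amend the outcome lists in the synopsis and in the section on primary and secondary outcome measures:

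- **All-cause events.** Report all-cause death and all serious adverse events, whatever their attribution, by arm, from randomisation to 30 days after the operation, or to 30 days after the scheduled date where there is none. The denominator is all randomised patients.
- **Surgery status.** Report by arm the number operated on as scheduled, delayed or not operated on, with reasons, separately from follow-up completion. Use this fraction when the full-trial size is revisited.
- **Postoperative morbidity.** Keep the 30-day outcome, labelled as a description of operated patients.

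The sample size of 88 is unaffected, and serious adverse events are already to be collected. The cost is one extra record check for unoperated patients, since the planned reviews on the date of surgery and 30 days later have no anchor without an operation, plus a surgery-status field with its reason and one more summary. The all-cause summary will not be directly comparable with the usual postoperative literature, which is why the existing outcome should stay beside it.

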## How will the outcome measures be measured at follow up?

The feasibility measures will be ascertained by the number of patients recruited and the number of patients completing follow-up as recorded on a standardized form by a research assistant, as well as patient reported compliance via a patient-completed diet diary that they will complete daily during the three-week period prior to surgery. Both the treatment and control arms will complete these forms and give them to the research assistant in an opaque envelope on the date of their surgery. Patients in the control arms will be instructed to leave the form blank.

Safety data will be ascertained via a combination of patient self-reporting and electronic medical record data. Paper and/or electronic questionnaires will be used to assess the presence of adverse events at baseline, the morning prior to surgery, and at 30-days postoperatively.

Similarly, efficacy data will be ascertained via review of the electronic medical record. Electronic medical records will be reviewed on the date of surgery and at 30-days postoperatively to assess for any further adverse events and to evaluate 30-day postoperative morbidity. We will assess operative time, intraoperative blood loss, and postoperative length of stay via electronic medical records. The quality-of-life data will be ascertained at baseline, following completion of the VLED, and at 30-days postoperatively via administration of an in-person paper or electronic SF-36 questionnaire. Lastly, anthropometric data (i.e., height, weight, waist circumference, grip strength) will be measured at baseline, the morning of surgery, and at 30-days postoperatively by a research assistant blinded to treatment allocation. This will be recorded and stored via a Redcap© form created *a priori*.

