## What are the proposed primary and secondary outcome measures?

Detailed criteria for event adjudication are reported in the associated documented titled “Trial Outcome Definitions”. An outcome adjudication committee will be formulated who will independently identify and report outcomes. This committee will be blinded to treatment allocation. Given that this is a pilot trial, the primary outcome will be feasibility.

Feasibility Outcomes:

1. Randomization percentage: Defined as the number of patients agreeing to participate in the RCT and being randomized to treatment or control divided by the number of patients approached for participation in the RCT. A randomization percentage of 70% or greater will support the feasibility of a full RCT. A lesser randomization percentage may be feasible with modifications.
2. Recruitment rate: Defined as the number of patients enrolled and randomized into the RCT per month. We will aim for a rate of 16 patients per month (i.e., 4 patients per site per month). A recruitment rate of equal to or greater than this will support the feasibility of a fully powered RCT. A recruitment rate of greater than 10 but less than 16 patients per month will be considered feasible with modifications for the larger RCT. A recruitment rate of less than 10 patients per month will suggest that a larger RCT is not feasible. For the full RCT, we anticipate participation of at least 10 sites. If each site recruited 4 patients per month, this would equate to 48 patients per year. Therefore, after 2.5 years of recruitment, we would reach our pre-specified sample size of approximately 1,200 patients.
3. Intervention compliance: Defined as the number of preoperative VLED doses taken divided by the total number of doses prescribed (84) for each participant randomized to the intervention arm. Compliance will be self-reported via written diet diaries (see “Study Diet Diary” document). A mean compliance of greater than 80% (i.e., completing 80% or more of their Optifast® 900 or Medimeal® doses), will be our benchmark for feasibility in the present study. A mean compliance between 70% and 80% will be considered feasible with modifications for the larger RCT. A mean compliance of less than 70% will suggest that a larger RCT is not feasible.

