## Are there likely to be any problems with compliance?

Adherence to a preoperative two-to-three-week regimen of preoperative VLED prior to bariatric surgery ranges from 80-90%.^51,52^ In our systematic review and meta-analysis evaluating the use of VLEDs in non-bariatric surgery, reported adherence ranged from 94-100% amongst the included studies, with much longer durations of intervention (0.46-24 weeks).^19^ As such, we feel as though compliance in the present study should be similar and is anticipated to range between 80% and 100%. In order to increase adherence with the study intervention, we will cover the cost of the Optifast® 900 or Medimeal® program and have patients complete a diet diary that they will submit following the three-week intervention period.

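### Compliance is defined over every patient randomised to the diet, but the diary that measures it is handed over on the day of surgery, with no stated route for patients who withdraw or are not operated on

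*Protocol*

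**What the plan says.** Protocol, *What are the proposed primary and secondary outcome measures?*, feasibility outcome 3, defines compliance as doses taken "divided by the total number of doses prescribed (84) for each participant randomized to the intervention arm". The synopsis repeats this definition. The same item names the source: "Compliance will be self-reported via written diet diaries". The criterion is the mean, with cut-offs at 80% and 70%.

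The timing of collection appears in three sections:

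- *How will the outcome measures be measured at follow up?*: patients in both arms "give them to the research assistant in an opaque envelope on the date of their surgery"; controls leave the form blank.
- *What is the proposed frequency and duration of follow up?*: "On the day of their surgery, patient data will also be collected with regards to compliance with the preoperative VLED". In the schedule under this heading, the row "Intervention adherence" is marked both for days -23 to -2 and for days -2 to 0. No method is given for the earlier mark.
- *Are there likely to be any problems with compliance?*: the plan is to "have patients complete a diet diary that they will submit following the three-week intervention period". Surgery is not mentioned.

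The automated platform, described under the arrangements for allocating participants, sends adherence reminders at weeks 1 and 2 and books a post-intervention appointment. Neither is linked to the diary or to a dose count.

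**The concern.** The population in the definition and the population reached by the collection procedure are not the same. The definition covers everyone randomised to the diet. The described handover reaches those who come to surgery. A diet patient who withdraws beforehand, or whose operation is cancelled or postponed, has no stated way to return a dose count.

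This matters because mean compliance is one of the primary feasibility criteria and decides whether the larger trial goes ahead unchanged, goes ahead with modifications, or does not go ahead. Patients who abandon the diet and leave the trial are those whose experience the criterion should capture. If their doses are never recorded, the analysis must either omit them or guess.

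**Working it through.** **Figures in the plan.** Four packets a day for three weeks is 4 × 21 = 84 doses, the stated denominator. The precision statement behind the sample size also reproduces: the Wilson interval for 90% of 88 is 82.0% to 94.7%, given as 82-95%. That calculation concerns follow-up completion; the sample-size section gives no calculation for compliance.

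**Inputs.** The diet arm has 44 patients (88 randomised 1:1; the budget justification also uses 44). The cut-offs are 80% and 70%. The protocol gives neither the number of missing diaries (k) nor the mean compliance of the patients concerned (c), so both are assumptions shown over a range. The returners' mean (m) is also assumed. The protocol anticipates 80% to 100%.

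**Formula.** Mean over all randomised diet patients = ((44 − k) × m + k × c) / 44.

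**Main illustration, m = 85%.**

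- k = 4, c = 0: (40 × 85) / 44 = 77.3%.
- k = 4, c = 30%: (40 × 85 + 4 × 30) / 44 = 80.0%, which is not above 80%.
- k = 9, c = 0: (35 × 85) / 44 = 67.6%.
- k = 9, c = 30%: (35 × 85 + 9 × 30) / 44 = 73.8%.

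**Range.** Whole-arm mean (%) by returners' mean:

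| Missing (k) | Their compliance (c) | m = 82 | m = 85 | m = 90 | m = 94 |
|---|---|---|---|---|---|
| 4 | 0 | 74.5 | 77.3 | 81.8 | 85.5 |
| 4 | 25% | 76.8 | 79.5 | 84.1 | 87.7 |
| 4 | 50% | 79.1 | 81.8 | 86.4 | 90.0 |
| 9 | 0 | 65.2 | 67.6 | 71.6 | 74.8 |
| 9 | 25% | 70.3 | 72.7 | 76.7 | 79.9 |
| 9 | 50% | 75.5 | 77.8 | 81.8 | 85.0 |

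If c equals m, nothing changes. With c = 0, the smallest number of missing diaries that brings the mean to 80% or below is 2, 3, 5 and 7 for m = 82, 85, 90 and 94%.

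**Direction.** A patient who stops the diet and withdraws has a low c, so leaving that patient out raises the mean. A patient whose operation is cancelled or postponed may have taken most or all doses, so leaving that patient out may raise the mean, lower it or leave it unchanged.

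**The case against.** A reader might infer that the protocol drops early stoppers from the mean, so that the go/no-go figure does read too high. The documents do not support that. No section says patients without a diary are left out. The definition names every randomised diet participant, and the scoring of a missing diary may be set out in a statistical analysis plan that is not shown. Averaging returned diaries alone is one way the gap could play out, not a stated rule.

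Other parts of the opposing case also stand:

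- Stopping the diet does not mean missing surgery. A patient who stops early but stays in the trial still hands over the diary on the day of the operation. Upward bias needs patients who both stop and withdraw.
- For a patient operated on as planned, the day of surgery is the first day after the diet, so the two collection rules agree. They part only when surgery does not happen on schedule.
- The counts of 4 and 9 are scaled to the protocol's 10-20% incomplete follow-up band, which is a broader measure: three visits, anthropometrics and questionnaires, in both arms. Four of 44 is 9.1%, just outside that band. Nine diet patients lost before surgery would by themselves put follow-up completion at 79/88 = 89.8%, already in the modifications band, so so large a loss would not pass unnoticed.
- The protocol cites adherence of 94-100% from its systematic review. At such levels a few missing diaries do not change the verdict.

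The objection does not remove the gap in collection. An analysis plan can say how to score a missing diary, but it cannot recover doses nobody recorded. Scoring them as zero would mark as non-compliant a patient who finished the diet before a cancelled operation. The adherence mark for days -23 to -2 has no method attached, and the week 1 and week 2 contacts are reminders.

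**Conclusion.** The point holds as a mismatch between definition and collection. Compliance is defined over all randomised diet patients; its only named source is collected on the day of surgery in two places and after the three-week period in a third; and patients who withdraw or are not operated on have no stated route.

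The effect is conditional. If only returned diaries are averaged, and the missing ones belong to patients who had stopped the diet, the mean reads too high. At an assumed 85% among returners, 4 missing of 44 are enough to lose the feasible verdict (77.3% at no doses, 80.0% at 30%). At 90% or more with 4 or fewer missing, it survives even if they took nothing (81.8% or higher). A firm claim of upward bias for cancelled or postponed operations would go beyond the documents. It is worth correcting before recruitment because it touches a primary feasibility criterion and cannot be repaired at analysis.

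**What to change.** 1. Reconcile the three collection statements (the two follow-up sections and the compliance section). The diary or dose count should be collected when the patient stops the diet or at the end of the diet period, whichever comes first, whether or not surgery takes place.
2. Protect the blinding. Use the same procedure in both arms, as the opaque envelope does now, or have the count taken by staff who do not make the blinded assessments.
3. Store any responses in the trial database. The protocol says the messaging platform keeps nothing but the email address, so it can prompt the patient but should not hold the answer.
4. In the definition of compliance, state that the mean is over all randomised diet patients. Report the number of missing diaries, and give the returners-only mean beside a conservative bound that counts undocumented doses as not taken. That bound should not be read as the best estimate, since it is biased downward for patients who took doses that were not documented.

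The cost is protocol wording, slight extra follow-up work for patients who leave early or are not operated on, and a compliance figure that may be less favourable. With 85% among returners and 4 missing, the bound lies 85 − 77.3 = 7.7 points lower; with many missing diaries the gap is wider.
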